#### Patient Datasets

Retrospective data will be available for all included patients (included population). Prospective data from the ePRO tool will be available for the subset of patients who complete the questionnaire (ePRO population).

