### Statistical Methods

#### Sample Size

This study aims to include all adults starting PAP therapy managed by an ALH home support provider in the participating countries who met the selection criteria during the study time period. This approach minimizes selection bias and sampling errors, ensuring precise and reliable results. Inclusions will be possible at the national level (France) or only at some investigational sites in countries requiring regional or hospital-level regulatory processes. All potential participants will be informed whenever ethics committee approval is obtained from the respective regions or hospitals. It is expected that around 30% of the 150,000 eligible participants will not be enrolled due to the absence of (or incorrect) email, or refusal to participate. Therefore, the number of included patients is expected to be around 100,000. With a sample of this size, the probability of showing a statistically significant difference in adherence between different levels of service if one exists is >99%, even if there were important imbalances between groups.

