#### Confounding Factors

Potential confounding factors were identified a priori based on a literature review and clinician expertise, and include age, sex, BMI, sleep duration, symptoms before starting PAP therapy, occupational status, highest education level, bed partner, comorbidities, smoking status, alcohol consumption, apnea-hypopnea index at the time of diagnosis, and prescriber specialty. Factors consistently described as being associated with PAP therapy adherence or persistence will be automatically included in statistical models comparing the effect of service on adherence or persistence. Other potential confounding factors will be selected based on their association with adherence or persistence in a univariate analysis. Full details of the confounding variables considered and the supporting sources are provided in Multimedia Appendix 2. Quantitative bias analysis will be performed to evaluate the impact of unmeasured confounders using a metric named the e-value [34]. The e-value can be defined as the strength of association that an unmeasured confounding factor would need to have in order to explain away the observed association.

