### Strengths

One of the major strengths of this study is its large sample size, which enhances the representativeness of the population and the generalizability of the findings. The retrospective design allows for long-term evaluation of PAP adherence and persistence and ensures that there is no influence on participants’ behavior because data were collected prior to their inclusion in the study. In addition, the AWAIR study will describe between-country differences in home provider services and patient characteristics for the first time, and report on patient satisfaction and experience with PAP therapy.

In contrast with conventional clinical trials, the real-world setting ensures that the results will reflect the usual course of care [56]. This is particularly important for evaluating adherence because it minimizes the risk of bias that could arise from study participation. Furthermore, real-world evidence is particularly relevant for meeting health authority post-approval effectiveness requirements [57]. Well-conducted comparative effectiveness research can provide valid results similar to randomized trials for this measure of known confounding factors [56], and can use methods (such as stratification, matching, or regression analyses) to account for or adjust for such factors and yield valid results [58]. In the real-world comparative AWAIR study, adjustment for potential confounders identified through literature review and clinical expertise, combined with the use of hierarchical models accounting for contextual differences related to the international nature of the study, will help the data to provide an accurate assessment of the net effect of home provider services on PAP adherence and persistence while minimizing the potential biases inherent in real-world studies. Additionally, the use of an ePRO tool facilitates the collection of data on confounding factors that would not otherwise be available in the retrospective database analysis, along with PROs, PREs, and health literacy across a large and diverse patient population from various geographic regions [59].

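### Eight of the 13 a priori confounders exist only for questionnaire completers, while the power and selection-bias statements refer to about 100,000 included patients

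*Protocol article*

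**What the plan says.** Patient Datasets defines two populations. For the first, "Retrospective data will be available for all included patients (included population". For the second, "Prospective data from the ePRO tool will be available for the subset of patients who complete the questionnaire (ePRO population".

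Confounding Factors lists 13 candidates: "age, sex, BMI, sleep duration, symptoms before starting PAP therapy, occupational status, highest education level, bed partner, comorbidities, smoking status, alcohol consumption", then apnea-hypopnea index (AHI) at diagnosis and prescriber specialty. Factors with consistent support in the literature are forced into the service models, and the others enter by univariate screening. Table 2 adjusts the main multilevel models for the selected factors and names no analysis population.

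Strengths states that the questionnaire "facilitates the collection of data on confounding factors that would not otherwise be available in the retrospective database analysis".

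Sample Size gives "It is expected that around 30% of the 150,000 eligible participants will not be enrolled", and so "the number of included patients is expected to be around 100,000". With that number, "the probability of showing a statistically significant difference in adherence between different levels of service if one exists is >99" percent, "even if there were important imbalances between groups". The same paragraph says that approaching every eligible patient keeps selection bias to a minimum.

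Limitations concedes that those who answer may differ from those who do not. The check it offers is a comparison of the study population with published sleep apnea data on age, sex and severity.

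**The concern.** The article makes its precision and selection claims for one population, while most of its adjustment set exists only in another. A standard mixed model that contains one questionnaire-only covariate drops every patient without a questionnaire, unless missing values are handled in some way.

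Lost precision is the smaller problem. According to Strengths, the adherence data were collected before inclusion. According to Limitations, the questionnaire comes at varying times, up to 5 years after the start of therapy. Completing it can therefore depend on the outcome. The route in also differs by country: a French patient is included by not objecting and must act only to become a completer, whereas patients in Portugal, Spain and Belgium must actively consent to be included at all. The Introduction says that service differs markedly between countries, so selection may vary along the exposure of interest. The results are meant to inform payers and tariffs, so a service effect distorted by who answered would matter.

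**Working it through.** **1. Source of each confounder (Confounding Factors against Table 1).**

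| Source in Table 1 | Factors | Count |
|---|---|---|
| Questionnaire only | sleep duration, pre-therapy symptoms, occupation, education, bed partner, comorbidities, smoking, alcohol | 8 |
| Provider records (ERP) | age, sex, BMI at start, AHI at diagnosis (BMI and AHI also in the questionnaire) | 4 |
| None listed | prescriber specialty | 1 |

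8 + 4 + 1 = 13.

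**2. The plan's own count.** 150,000 × (1 − 0.30) = 105,000, against about 100,000 stated. The stated figure implies a loss of 33.3%. Both inputs are approximate, so this is rounding and not an error.

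**3. Completers.** The article gives no completion rate. Per 100,000 included, assumed rates of 10%, 20%, 30% and 40% leave 10,000, 20,000, 30,000 and 40,000. The standard error ratio is √(100,000/n): √2.5 = 1.58 at 40,000 and √10 = 3.16 at 10,000.

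**4. Power.** The >99% cannot be reproduced, because no effect size, adherence rate, SD or group share is given. Assumed here: two-sided 0.05, 10:90 split, 70% adherent in the reference group, SD 2 h/day, no clustering.

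For proportions, power = Φ[(|p₁ − p₀| − 1.96·SE₀)/SE₁], with SE₀ pooled and SE₁ unpooled. Example, 73% against 70% at N = 20,000 (2,000 and 18,000): SE₀ = √[0.703 × 0.297 × (1/2,000 + 1/18,000)] = 0.01077; SE₁ = √(0.73 × 0.27/2,000 + 0.70 × 0.30/18,000) = 0.01050; Φ[(0.03 − 0.02111)/0.01050] = Φ(0.85) = 80%. For means, power = Φ[δ/SE − 1.96], with SE = 2√(1/n₁ + 1/n₀).

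| N | 73% vs 70% | 72% vs 70% | 0.2 h/day |
|---|---|---|---|
| 100,000 | >99.9% | 98.7% | >99.9% |
| 30,000 | 93% | 62% | 99.9% |
| 20,000 | 80% | 46% | 98.9% |
| 10,000 | 50% | 26% | 85% |

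**5. Bias, proportion adherent.** With true adherence p and response rates a (adherent) and b (non-adherent), adherence among completers is p·a/[p·a + (1 − p)·b]. Response rates are assumed.
- No true effect, p = 0.70 in both groups. Response 30%/15% gives 0.210/(0.210 + 0.045) = 82.4%. Response 60%/50% gives 0.420/(0.420 + 0.150) = 73.7%. The spurious gap is 8.7 points.
- True 75% against 70%, response 30%/15% in both groups: 0.225/0.2625 = 85.7% against 82.4%. A 5.0-point effect shrinks to 3.4.

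**6. Bias, hours per day.** Assumed: normal use h, mean 5.0 (lower service) and 5.3 (higher service), so the true effect is 0.30. Response follows logit π(h) = logit(r) + g(h − 5), where r is the response rate at 5 h and g the gradient per hour. The completer mean is ∫h·f(h)·π(h)dh / ∫f(h)·π(h)dh, integrated numerically.

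| g lower / higher service | SD | r = 10% | r = 30% | r = 50% |
|---|---|---|---|---|
| 0.35 / 0.35 | 2 | 0.282 | 0.271 | 0.270 |
| 0.35 / 0.30 | 2 | 0.140 | 0.176 | 0.201 |
| 0.35 / 0.20 | 2 | −0.173 | −0.042 | 0.044 |
| 0.35 / 0.20 | 1.5 | 0.016 | 0.088 | 0.144 |
| 0.20 / 0.35 | 2 | 0.750 | 0.604 | 0.515 |

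Equal gradients do little harm. Unequal gradients can shrink or inflate the effect. Reversal needs a wide gap in one direction, together with SD 2 and a low to moderate response.

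**The case against.** The article never says that the main models run on completers. It defines two populations and assigns neither, speaks of selected confounders, and leaves the forced set to an appendix that is not shown. A statistical analysis plan could adjust for provider-record factors only, or impute, and so keep everyone. This stands: a reader might infer that the main models silently drop all non-completers, but the documents do not establish it. What they do establish is conditional: without imputation, adjusting for any of the eight factors leaves completers only. That condition is likely to be met, since the univariate screen works on very large numbers, and Table 2's third objective enters sociodemographic and clinical characteristics, a category with several questionnaire-only items.

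A reader might also infer that completers are the satisfied, persistent users, or that completion always comes years later. Neither is stated. Limitations says only that responders might differ, and 5 years is the maximum: a late-2023 starter in France could be invited from October 2024, within a year. Nor is sign reversal the expected result; it sits in one corner of step 6.

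Power is also less fragile than it may seem. For 0.2 h/day it is still 98.9% at 20,000.

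Finally, inclusion itself follows the outcome and differs by country, so the included population is selected too. A model with provider-record covariates alone trades possible selection bias for known under-adjustment. Which model should lead is a matter of judgement.

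**Conclusion.** The point holds as a mismatch between populations. The source count is firm and Strengths confirms it. The >99% power and minimal selection bias are claimed for about 100,000 patients, and a fully adjusted model without imputation cannot use them all. This is more than detail left to an analysis plan, because the article makes claims for one population that its own adjustment set may not support.

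The main risk is selection related to the outcome and differing by country or service level. Its size is unknown: the 8.7-point gap and the −0.17 to 0.75 h/day range around a true 0.30 come from assumed response patterns. Existing safeguards do not reach it. The comparison with published data looks at age, sex and severity and cannot detect selection on adherence, the e-value addresses unmeasured confounding, and the sensitivity analyses concern COVID-19 and the device recall. The data that would show selection among included patients, device and provider records on non-completers, are already held.

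**What to change.** - Name the analysis population for each model.
- Report the model adjusted for provider-record factors (age, sex, BMI at start, AHI at diagnosis) in all included patients beside the fully adjusted model in completers. Neither need be the headline.
- Refit the provider-record model in completers, so that the effect of selection is separated from that of fuller adjustment.
- Weight the completer model by the inverse probability of completion, estimated from provider and device data including use and persistence, or use multiple imputation.
- Compare completers with non-completers on those data, by country and service level.
- State the expected completer count, and restate the power and selection-bias claims for it.

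The cost is extra models on data already held. None of this removes selection at the consent stage, which differs between France and the other three countries and should be stated as a remaining limitation.

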#### Multilevel Models

Individuals living in the same country share a common health care system, lifestyle, and climate, and tend to be more similar than individuals from other countries. Therefore, individuals are considered nested within a country. This correlation of observations violates the assumption of independence for standard regression analysis leading to biased standard errors of parameter estimates. Therefore, we will fit multilevel linear or logistic mixed models using the country variable as a random effect to test the association between adherence or persistence and levels of service while accounting for this nested data structure.

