## Abstract

**Background:**

Adherence and persistence to positive airway pressure (PAP) therapy are key factors for positive health outcomes. Home support providers participate in the home implementation and follow-up of PAP therapy for patients with obstructive sleep apnea (OSA). In Europe, home support provider service levels are country (or area) specific, resulting in differences in content and frequency of patient interactions. However, no robust evaluation of the impact of these differences on clinical and patient outcomes has been performed.

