## Introduction

Obstructive sleep apnea (OSA) is the most prevalent form of sleep-disordered breathing, affecting nearly 1 billion adults aged 30-69 years worldwide [1]. OSA is characterized by repetitive collapse of the upper airway during sleep, resulting in complete (apnea) or partial (hypopnea) airway obstruction [2]. OSA can cause daytime symptoms that impair quality of life and has been linked with a variety of cardiometabolic diseases, neurocognitive impairment, depression, road traffic accidents, and all-cause mortality [3-12]. Identification and management of OSA are therefore important to reduce those risks.

Positive airway pressure (PAP) therapy remains the gold standard treatment for severe OSA because high-quality evidence and long-term assessment are lacking for noncontinuous PAP therapies [13,14]. PAP therapy has been shown to reduce road traffic accidents, blood pressure, cardiovascular risk, and health care use [15-19]. However, the effectiveness and cost-effectiveness of PAP therapy are linked to sufficient daily device use, with regular and continued long-term usage [16,19-24], which appears challenging in all geographies [25,26].

In most European countries, home support provider companies supply the PAP device and support its use by the patient. However, the type and level of services provided differ markedly between countries. Services can range from mainly logistical support (ie, device delivery in Belgium, Germany, and the Netherlands) to a personalized support plan for patients integrating motivational interviews to enhance adherence (as in some regions of Spain and Portugal) [27-29]. Also, the number of regulated home visits varies from none to several per year (like in France and Portugal). The use of PAP telemonitoring also varies widely, being routine for almost all patients in France throughout the PAP treatment period [30] but not used (or only used in the first months of therapy or in specific situations) in other countries. Criteria for the reimbursement of PAP therapy also differ markedly between European countries and are likely to influence adherence and persistence. For example, while the fees paid to the home support providers in France increase as the number of hours of PAP use increases [30,31], in Belgium and Germany, nonadherence can result in the cessation of patient reimbursement.

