## Methods

### Study Design

This international, ambispective, real-world, cohort study is being conducted in 4 European countries (France, Belgium, Spain, and Portugal). It includes a retrospective analysis with the reuse of home support provider data routinely collected for PAP-related services and a prospective evaluation with the collection of patient data using a web-based patient questionnaire.

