#### Statistical Analysis

Statistical analyses will be performed according to a predefined statistical analysis plan (Table 2).

**Table 2 table2:** Statistical analysis plan details.

Objectives	Main outcomes	Key explanatory variables	Statistical methods
Compare PAP^a^ adherence and the PAP therapy persistence rate between different levels of home support provider service	PAP adherence: (1) mean number of hours/day of PAP use and (2) adherent patients defined as those with mean PAP use ≥4 hours/day PAP persistence: (1) percentage of days with PAP use, (2) patients still in therapy, and (3) patients still in therapy and adherent	Fixed effect: Level of service (standard of care, personalized care plan, or high service level) Random effect: Country	Multilevel model adjusted for selected confounding factors
Identify service components that influence PAP adherence and persistence	PAP adherence: (1) mean number of hours/day of PAP use and (2) adherent patients defined as those with mean PAP use ≥4 hours/day PAP persistence: (1) percentage of days with PAP use, (2) patients still in therapy, and (3) patients still in therapy and adherent	Fixed effect: Frequency of interactions, content of support, personalization of support, and telemonitoring Random effect: Country	Multilevel model adjusted for selected confounding factors
Identify factors associated with PAP adherence and persistence	PAP adherence: (1) mean number of hours/day of PAP use and (2) adherent patients defined as those with mean PAP use ≥4 hours/day PAP persistence: (1) percentage of days with PAP use, (2) patients still in therapy, and (3) patients still in therapy and adherent	Fixed effect: Frequency of interactions, content of support, personalization of support, telemonitoring, sociodemographic characteristics, OSA^b^-related clinical characteristics, and characteristics of PAP therapy Random effect: Country	Multilevel model
Descriptive Analysis	Sociodemographic characteristics OSA-related clinical characteristics OSA and PAP literacy Experience with PAP therapy Experience with home support provider support Quality of life Home support provider PAP-related service	N/A^c^	Usual descriptive statistics: Analysis by country
Describe patterns of PAP use	Mean PAP use categories over time	N/A	Data visualization such as Sankey diagrams

^a^PAP: positive airway pressure.

^b^OSA: obstructive sleep apnea.

^c^N/A: not applicable.

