### Opportunities

Clinical trials are critical in the assessment of health products and services. However, managing and executing randomized controlled trials pose significant challenges in terms of inclusion, data collection, follow-up, comparator group, and costs [61]. Specifically in patients with OSA treated with PAP, it was shown that recruitment strategies in randomized trials could result in a lack of representativeness of the participants, because only up to 20% of typical patients with OSA meet the eligibility criteria, limiting the generalizability of the results [62]. The expanding availability of real-world data combined with advancements in operational tools and methodologies presents a significant opportunity to develop alternative study designs that leverage existing data. Furthermore, the European Health Data Space will create a common framework in Europe for the reuse of health data for research [63]. The design of the AWAIR study integrates multiple real-world data sources (including operational databases, device data, and an ePRO tool), the use of comparative real-world methods, and the implementation of e-consent. This innovative approach not only makes the study more robust but also sets a precedent for future research in similar fields, particularly regarding the number of participants who will consent and complete the ePRO tool. The design allows the study to be continuously enriched with data from new countries to measure the effect of other service levels and also to extend patient follow-up to assess longer-term persistence or include other patients in the countries of interest to assess the impact of changes in service levels.

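### Service is set by country or area, but the model's only clustering term is a random intercept for four countries, so between-country contrasts do not give a net service effect and area-level dependence is left out

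*Protocol article*

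**What the plan says.** The Abstract (Background) states that "home support provider service levels are country (or area) specific". The Introduction gives examples of both kinds: country-wide differences, such as mainly logistical support in Belgium and near-universal telemonitoring in France, and "a personalized support plan for patients integrating motivational interviews to enhance adherence (as in some regions of Spain and Portugal").

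The study is "conducted in 4 European countries (France, Belgium, Spain, and Portugal"). For the main objective, Table 2 sets "Fixed effect: Level of service (standard of care, personalized care plan, or high service level) Random effect: Country". Country is also the only random effect in the other two model-based objectives. The Multilevel Models section confirms this: "we will fit multilevel linear or logistic mixed models using the country variable as a random effect". It treats patients as nested in a country and in nothing smaller. Its stated reason is that ignored correlation biases standard errors.

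On national context, the Introduction says: "Criteria for the reimbursement of PAP therapy also differ markedly between European countries and are likely to influence adherence and persistence". It cites provider fees that rise with hours of use in France, and reimbursement that can end with nonadherence in Belgium. The factors named under Confounding Factors are patient characteristics plus prescriber specialty; none is a payment rule.

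The Strengths section nevertheless expects that adjustment and hierarchical models will help to "provide an accurate assessment of the net effect of home provider services on PAP adherence and persistence". The Abstract (Methods) also refers to the net effect.

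**The concern.** A random effect protects inference about an exposure only if it sits at the level where the exposure is set, and only if that level has enough units. The article names two such levels, country and area, and models one. At country level there are four units, and service moves together with payment and care rules. At area level, patients who share a service arrangement are treated as independent once the country is known.

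At stake is the main objective. The Study Rationale aims the results at payers and authorities reassessing services and tariffs. A difference caused by a payment rule, or by a handful of areas, could be presented to them as a benefit of service.

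**Working it through.** **Inputs.** From the article: four countries, three service levels in Table 2, country as the only random effect, about 100,000 patients. Not in the article, hence assumed: intraclass correlations (ICC), patients per area, outcome SD, test reference distribution, number of areas, patient split by country. A two-sided 5% level is used throughout.

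**The plan's own figure.** The only related figure is power above 99% (Sample Size). No effect size, SD, alpha, allocation or ICC is given, so it cannot be strictly reproduced. With 100,000 independent patients and an assumed SD of 2.5 h/day, a difference of 0.25 h/day has power of about 100% with 5% of patients in the smaller group, and 88% with 1%. The figure is thus attainable if patients are independent; it says nothing about clustering.

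**(a) Service constant within a country.**
- Residual degrees of freedom: 4 − 2 = 2 for two service levels; 4 − 3 = 1 for three.
- If a Wald statistic is referred to the normal value 1.96: P(|t₂| > 1.96) = 0.189 and P(|t₁| > 1.96) = 0.300.
- A simulation of a country random-intercept model (REML, Wald z test, 2,000 datasets per setting, country ICC 0.005 to 0.05) gave 18% to 20% and 27% to 30%.
- The country variance does enter the standard error here. With two countries against two, τ² = ICC × 2.5² and 50,000 patients per side, SE = √[τ²(1/2 + 1/2) + 2.5²(1 − ICC)(2/50,000)]. This gives 0.081 h/day at ICC 0.001, 0.250 at 0.01 and 0.559 at 0.05, against 2.5 × √(4/100,000) = 0.016 for independent patients.
- No choice of test removes the second difficulty. A service level found throughout a country, and a payment rule found throughout the same country, are the same column of data.

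**(b) Service varying by area within a country.** If everyone in an area has the same service, the design effect is D = 1 + (m − 1) × ICC, for m patients per area. Omitting the area term makes the standard error too small by √D, and the false-positive rate is 2 × P(Z > 1.96/√D).

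| Area ICC | m = 200 | m = 500 | m = 1,000 |
|---|---|---|---|
| 0.005 | D 2.00, 17% | D 3.50, 29% | D 6.00, 42% |
| 0.01 | D 2.99, 26% | D 5.99, 42% | D 10.99, 55% |
| 0.02 | D 4.98, 38% | D 10.98, 55% | D 20.98, 67% |

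In the central case, √5.99 = 2.45 and 2 × P(Z > 0.80) = 0.42. A simulation with other assumptions (6 areas in Spain with about 1,667 patients each, 4 in Portugal with 1,250 each, country ICC 0.01) gave 5.6% at area ICC 0, 22% at 0.001, 51% at 0.005, 63% at 0.01 and 74% at 0.02.

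**How far country confounding reaches.** For service that varies within a country, a random intercept with very large clusters acts almost like a fixed effect. The relative weight left to between-country information is about 1/[1 + m × ICC/(1 − ICC)]. With 25,000 patients per country and ICC 0.01 (both assumed), this is 1/(1 + 252.5) = 0.4%; with 3,000 patients it is about 3%. Confounding by national rules is therefore mainly a problem of part (a).

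**The case against.** Several points on the other side are sound and limit the finding.

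- A reader might infer that all the standard errors ignore the level of assignment, or that a four-country comparison will come out with very narrow intervals. Neither follows: for country-constant service the country term is at the right level and widens the interval.
- A reader might infer that the plan has a 19% or 30% error rate. The article states no test or degrees-of-freedom method, and the statistical analysis plan is not shown. Those rates are conditional on a normal reference.
- A reader might infer that national payment rules will contaminate every service estimate. The weights above show that this does not hold for within-country contrasts.
- The article does not assign the three service levels to countries or areas. Outcome Measures counts personalization to the patient as a service component, and Table 1 lists interactions and telemonitoring over time. If service varies between patients within an area, the inflation in (b) is smaller. The phrase about regions of Spain and Portugal could also mean regions of Spain plus the whole of Portugal.
- The wording is partly cautious. Multilevel Models speaks of association, and Strengths says the methods will help towards the net effect. E-values are planned, and Limitations admits residual confounding.

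These do not remove the core. Table 2 and Multilevel Models fix the random structure, so this is not a detail left to another document. The e-value neither corrects standard errors nor separates service from country. Sensitivity Analyses cover only COVID-19 lockdowns and the device recall. Limitations does not mention confounding of service with country or area. The Opportunities remark, "The design allows the study to be continuously enriched with data from new countries to measure the effect of other service levels", is not an error in itself, but it shows that between-country contrasts are meant to inform on service.

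**Conclusion.** The point holds in two limited parts. First, for service levels constant within a country, the planned model yields a comparison of countries together with their service packages, on 2 or 1 residual degrees of freedom, and not a net service effect. This follows from the article alone; the 19% to 30% false-positive rate additionally assumes a normal-reference test. Second, for service set by area within a country, the stated model omits the level of assignment and its standard errors are too small. The 17% to 67% range illustrates how much this could matter. It rests on the assumed ICC, area size and uniform service within areas, and is not an estimate for this study. How many service levels fall under each part cannot be told from the article.

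**What to change.** 1. State for each service category, and each component in the second objective, whether it varies by country, area or site, or patient.
2. Enter country as a fixed effect.
3. Add a random effect for the area or site at which service is set, or use cluster-robust errors at that level. Either needs a small-sample correction suited to both linear and logistic models, since the main outcomes in Table 2 include both types.
4. Base claims about the effect of service on within-country contrasts.
5. Report contrasts that exist only between countries as *country plus service package* associations.
6. Reword the net-effect statements in the Abstract (Methods) and Strengths to match, and name the confounding of service with country under Limitations.

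The cost is wider intervals and no net-effect estimate for service levels that never coexist within a country. A country with uniform service adds nothing to the within-country estimate; if that were France, where about 90,000 patients have been informed, the loss of information would be large. The article does not list area, hospital or agency among the variables taken from the provider systems, so the sponsor must confirm that such identifiers are available in the study database. If they are, the change is one of model specification and wording only.
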